#### Data management

All researchers including therapists, data collector, data entry clerks, data manager, statistician, and outcome assessors will receive training regarding the data management. Upon conclusion of the treatment period, all participant data will be completed and recorded on the original case report forms (CRFs). The data will be entered into Excel spreadsheets by two separate data entry clerks, following which the data manager will compare the accuracy of the two datasets. If any differences are noted, corrections will be made according to the original CRFs.

All paper files related to the research will be saved and electronic documents will be stored in a password-protected computer. All research documents, including both the paper files and electronic documents, will be preserved for at least five years after publication. If readers have any questions regarding our published data, they will be permitted to contact our first author or corresponding author to ask for the original data. The private information of patients including name, age, and telephone number, will be protected and never disclosed to anyone.

In addition, we will establish an independent Data and Safety Monitoring Board (DSMB) to review and interpret data generated from the study (Additional file 3). The primary objective of DSMB is to ensure the integrity of the research data. The DSMB will review the progress of the trial and decide on any premature closure of the study.

#### Sample size

This pilot study aims to assess the efficacy of acupuncture for PDS as well as the feasibility of a further large clinical trial. We did not perform a sample size calculation for this pilot study, but will use a convenience sample based on the known availability of study participants at the three sites. We estimate that we will be able to enroll 42 individuals, 14 in each center, for this pilot study. Both the verum acupuncture and minimal acupuncture groups will contain 21 eligible participants. The outcomes of this study will facilitate the calculation of the appropriate sample size for further RCTs.

#### Statistical analysis

The statistical analysis will be performed by an independent statistician who is blinded to group allocation using SPSS 19.0 (IBM SPSS Statistics, New York, NY, USA). All efficacy analyses will be performed using the intent-to-treat (ITT) and per-protocol (PP) population. For ITT analysis, the population will consist of all participants who have been randomized and received acupuncture treatment at least once and the last observation carried forward rule will be applied. The PP analysis will include only those participants who will complete more than ten acupuncture treatments and have no major protocol violations (taking other drugs during the trial, not completing the CRF as required, etc.). The categorical data will be described as percentage (n %) and continuous data using mean ± standard deviations. Continuous variables will be analyzed using the t-test and categorical variables using the Chi-square (χ^2^) test. The statistical significance level will be set at 0.05 (two-sided) with 95% confidence intervals.

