#### Randomization and allocation concealment

All participants who meet the inclusion criteria will be randomly assigned to the verum acupuncture group or minimal acupuncture group in a 1:1 ratio according to a randomization sequence generated using SPSS19.0 software. The randomization sequence will be prepared by a professional statistician, who will not be involved in assessment or treatment of participants. An independent clinical trials researcher will implement the allocation schedule using a centralized telephone randomization procedure. The random number will be assigned after the participants have met all inclusion criteria and completed baseline assessment. The Clinical Research Coordinator (CRC) will be responsible for enrolling participants, obtaining informed consent and requesting randomization.

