#### Blinding

The acupuncturists who deliver the treatment to the participants will not be blind to treatment allocation. Blinding of acupuncturists is not possible due to the nature of acupuncture. Participants and all other investigators will be blinded to the treatment allocation, including the data analysis and outcome assessors. Treatment groups will be identified as Group A and Group B during the statistical analysis of all the data for data analysis.

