#### Primary outcome measurement

The primary outcome is the responder rate based on the overall treatment effect (OTE) at end-of-treatment (EOT, four weeks after randomization) [26, 27]. The patient will be asked to decide whether symptoms have changed compared with pre-treatment using a Likert scale. The question will be asked “How were your gastric symptoms during the past week in comparison with the baseline period?” The seven-point Likert scale consists of “extremely improved,” “improved,” “slightly improved,” “not changed,” “slightly aggravated,” “aggravated,” and “extremely aggravated” [27]. Patients who are “extremely improved” or “improved” of the OTE will be considered responders. OTE has been used as the primary and secondary outcomes measure in several trials with FD [27–31]. The advantage of this endpoint is that it closely resembles the way physicians evaluate treatment benefit in clinical practice, but the main disadvantage is the inherent recall of pre-treatment symptom severity which may lead to bias [26].

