## Discussion

People with PDS have a normal life expectancy, but the impact on QoL is notable. This pilot study has been designed, therefore, to evaluate whether acupuncture will improve the symptoms of PDS (postprandial fullness and early satiation) and be a feasible therapy for clinical treatment.

Whether different treatments are needed for EPS and PDS is indistinct and in the previous RCTs, only acotiamide, a new drug for the treatment of FD, has been certified to be effective in PDS but not in EPS [30]. We are the first RCT designed for PDS with acupuncture treatment. Our study meets methodological theory of adequate randomization and allocation concealment, blinding of outcome assessors and statisticians, and applying ITT analysis strategy. In addition to PDS symptoms and disease-specific QoL, the depression and anxiety status of the patients will also be measured in our study.

The primarily limitation of our trial is that acupuncturists could not be blinded, but we provided special training and provide a brochure to minimize bias. Second, in consideration of the ethical requirements and patient compliance, a blank control group was not designed and the influence of self-healing could not be excluded from the acupuncture effect. This pilot RCT aims to evaluate the feasibility and efficacy of acupuncture for PDS and, if effective, a further large clinical will be conducted.

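### The set labelled ITT leaves out randomised participants who attend no session, so no planned efficacy analysis includes everyone randomised, although the Discussion claims an ITT strategy

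*Protocol article*

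**What the plan says.** The Statistical analysis section names two efficacy sets: "All efficacy analyses will be performed using the intent-to-treat (ITT) and per-protocol (PP) population". It defines the first by two conditions: "For ITT analysis, the population will consist of all participants who have been randomized and received acupuncture treatment at least once". For missing data within that set, "the last observation carried forward rule will be applied". The second set is more restrictive: "The PP analysis will include only those participants who will complete more than ten acupuncture treatments", and it also requires the absence of major protocol violations.

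On timing, Randomization and allocation concealment states: "The random number will be assigned after the participants have met all inclusion criteria and completed baseline assessment". On blinding, the article says that participants and all other investigators do not know the allocation, but "The acupuncturists who deliver the treatment to the participants will not be blind to treatment allocation".

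The endpoint is binary: "The primary outcome is the responder rate based on the overall treatment effect (OTE) at end-of-treatment", four weeks after randomisation. The Discussion then counts among the trial's methodological merits "blinding of outcome assessors and statisticians, and applying ITT analysis strategy", with no qualification.

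**The concern.** Intention-to-treat means that everyone randomised is analysed in the arm assigned. Receiving a first session happens after randomisation, so making it a condition of entry turns the set into a modified ITT (treated) set. This is a rule that the article states and labels wrongly, not a detail left to another document.

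Two things are at stake. First, a reader of the Discussion would take the comparison to rest on all randomised participants, and it does not. Second, exclusion after randomisation is not guaranteed to be unrelated to arm, because the person giving the first session knows the allocation. The arms are small, so even one exclusion shifts a responder rate visibly. Those rates are also meant to inform the size of a later trial.

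**Working it through.** The article gives no figure to reproduce for this point. The check has two parts.

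**1. Definitions side by side**

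- Randomisation follows eligibility and baseline assessment and precedes the first session. A randomised participant with zero sessions is therefore possible.
- The set called ITT requires at least one session, so that participant is out.
- The per-protocol set requires more than ten sessions, so that participant is out there too.
- Last observation carried forward acts only on people already in the set and brings nobody back. Table 3 schedules the OTE at weeks 1 to 4, 8, 12 and 16 but not at baseline. For someone with no post-randomisation OTE there is nothing to carry forward.
- Hence no planned efficacy analysis includes everyone randomised, and the Discussion's claim does not match the definition.

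**2. How much one exclusion can matter**

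Inputs from the article: 42 participants, 21 per arm (Sample size); chi-square test, two-sided 0.05 (Statistical analysis).

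Assumed inputs: 13 verum and 7 minimal-arm responders, and the number *k* of participants with no session. The article gives neither. Untreated participants are taken to be non-responders.

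Share of an arm lost: *k*/21, which is 1/21 = 4.8%, 2/21 = 9.5% and 3/21 = 14.3%.

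Uncorrected Pearson chi-square for a 2×2 table with cells a, b (verum responders, non-responders) and c, d (minimal-arm responders, non-responders):

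X² = N(ad − bc)² / [(a+b)(c+d)(a+c)(b+d)]

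- All randomised, 13/21 v 7/21: 42 × (13×14 − 8×7)² / (21×21×20×22) = 42 × 126² / 194,040 = 3.436, p = 0.064.
- One untreated verum non-responder dropped, 13/20 v 7/21: 41 × (13×14 − 7×7)² / (20×21×20×21) = 41 × 133² / 176,400 = 4.111, p = 0.043.
- One untreated minimal-arm non-responder dropped, 13/21 v 7/20: 41 × (13×13 − 8×7)² / (21×20×20×21) = 41 × 113² / 176,400 = 2.968, p = 0.085.

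| Table | Verum | Minimal | Difference (points) | p, uncorrected | p, continuity-corrected | p, Fisher |
|---|---|---|---|---|---|---|
| 13/21 v 7/21 | 61.9% | 33.3% | 28.6 | 0.064 | 0.122 | 0.121 |
| 13/20 v 7/21 | 65.0% | 33.3% | 31.7 | 0.043 | 0.086 | 0.063 |
| 13/19 v 7/21 | 68.4% | 33.3% | 35.1 | 0.027 | 0.057 | 0.056 |
| 13/21 v 7/20 | 61.9% | 35.0% | 26.9 | 0.085 | 0.158 | 0.121 |

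One exclusion changes the difference in responder rates by about 3 points up (verum) or about 2 points down (minimal arm).

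**The case against.** The strongest reply is that the defect may never bite. The two sets differ only if someone is randomised and then attends no session, and the article gives no such number. The window is narrow, because randomisation waits for consent, eligibility and baseline assessment. Participants are blinded, so a person who fails to appear for the first session should not know the arm. For the loss to depend on arm, an unblinded acupuncturist would have to influence whether the first session takes place, and nothing in the article suggests that. This stands, and it limits the size of the concern. It does not make the label or the Discussion's claim correct.

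The p-values also need care. The counts were chosen close to 0.05. With a continuity correction or Fisher's exact test, neither one nor two verum exclusions crosses the line in this example, and the article does not say whether a correction applies. Crossing 0.05 is also a weak measure of harm in a 42-person pilot on a convenience sample. The example shows sensitivity, not a likely result.

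A reader might infer more than the text supports:

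- **That randomisation no longer protects the comparison.** This does not follow when the exclusions may be none or few and participants are blinded.
- **That dropout will be understated.** An efficacy set does not determine how attrition is reported, and the article says the protocol conformed to CONSORT.
- **That failing to name ITT or per-protocol as primary is a further fault.** That choice may sit in a statistical analysis plan that is not shown.

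**Conclusion.** The point holds as a fault of definition and labelling. The set called ITT is a modified ITT set, the per-protocol set is narrower, no planned efficacy analysis retains everyone randomised, and the Discussion's claim is not delivered. That conclusion rests on the article's wording alone.

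The likely bias is small, and it is nil if every randomised participant attends at least one session. If some do not, each one is 4.8% of an arm and can move the result in either direction: in the assumed example, from an uncorrected p of 0.064 to 0.043 or to 0.085. Those values depend on the assumed responder counts, on treating untreated participants as non-responders, and on the uncorrected test.

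**What to change.** Define ITT as all randomised participants, analysed in the arm to which they were assigned. For the responder outcome, count as non-responders those with no post-randomisation OTE, since for them there is no observation to carry forward. This can leave the stated carry-forward rule in place for treated participants who drop out after giving an OTE. Counting every missing OTE as non-response would replace that rule, which is a separate decision and is not needed here.

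If the treated-at-least-once set is kept, call it modified ITT, use it as a sensitivity analysis, and make the Discussion agree with the sets as finally defined.

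The cost is a few sentences. Treatment and visit schedules do not change, and because the trial is still recruiting, the definition can be settled before analysis. The downside is that responder rates may be slightly lower, because untreated participants stay in the denominator.

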### Secondary outcome measurements

#### Global assessment at other time-points

The primary outcome measurement is the OTE at the EOT; however, responder rate based on OTE will also be measured weekly (during the treatment) and at weeks 8, 12, and 16 after randomization with a seven-point Likert scale [27].

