#### Disease-specific QoL assessment

QoL will be assessed at baseline and at weeks 4, 8, and 16 after randomization using the 25-item Nepean Dyspepsia Index (NDI) [32–34], which measures the specific life quality of FD patients in four domains: interference (13 items); know/control (seven items); eat/drink (three items); and sleep/disturb (two items). The scores are measured using a five-point Likert scale that ranges from “not at all” to “extremely,” with higher scores indicating a better QoL.

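### Last observation carried forward in the ITT analysis leaves the week-4 OTE undefined for participants who leave before week 1, counts part-treatment ratings as end-of-treatment results, and assumes persistence at follow-up

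*Protocol article*

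**What the plan says.** Protocol article, Statistical analysis: "All efficacy analyses will be performed using the intent-to-treat (ITT) and per-protocol (PP) population". The ITT set is everyone randomized who "received acupuncture treatment at least once and the last observation carried forward rule will be applied". No other handling of missing values is stated. The second population is narrower: "The PP analysis will include only those participants who will complete more than ten acupuncture treatments and have no major protocol violations", and an incompletely filled case report form is listed among those violations.

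Primary outcome measurement: "The primary outcome is the responder rate based on the overall treatment effect (OTE) at end-of-treatment (EOT, four weeks after randomization"). The question put to the patient is "How were your gastric symptoms during the past week in comparison with the baseline period", and "Patients who are “extremely improved” or “improved” of the OTE will be considered responders".

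Global assessment at other time-points: "responder rate based on OTE will also be measured weekly (during the treatment) and at weeks 8, 12, and 16 after randomization". Table 3 agrees and shows no OTE at baseline. For the Nepean Dyspepsia Index (NDI), "QoL will be assessed at baseline and at weeks 4, 8, and 16 after randomization"; HADS follows the same schedule. The eight symptom scores are taken at baseline, at weeks 1 to 4, and at weeks 8, 12 and 16.

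**The concern.** One carry-forward rule is applied to outcomes with different schedules and different meanings, and it makes a different assumption about dropouts in each.

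- **OTE at week 4.** A change rating has no baseline value to fall back on, and membership of the ITT set requires one treatment but no rating. Where a rating does exist, it may have been made early in the course and is then read as the result of the full course.
- **OTE and symptoms at weeks 8, 12 and 16, and NDI and HADS at weeks 8 and 16.** Treatment has ended. Carrying the week-4 value forward supplies by assumption the durability that these visits were scheduled to observe.
- **NDI and HADS at week 4.** Nothing is collected between baseline and week 4, so an earlier dropout is recorded as unchanged. The same person may be a responder on OTE if an early rating was favourable.

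At stake are the week-4 responder rate, which is meant to inform the size of a later trial (Sample size), and any statement about how long a benefit lasts.

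**Working it through.** **Inputs from the Protocol article.** 42 participants, 14 at each of three centers, 21 per arm (Sample size); 12 sessions over four weeks, three per week (Intervention); OTE at weeks 1, 2, 3, 4, 8, 12 and 16 (Table 3); chi-square test, two-sided 0.05 (Statistical analysis). The plan's own figure reproduces: 3 × 14 = 42 = 2 × 21. There is no power calculation, effect size or dropout rate to check.

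**What the rule yields, by time of leaving (after at least one treatment)**

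| Last visit attended | OTE used at week 4 | Sessions scheduled by then | NDI/HADS used at week 4 |
|---|---|---|---|
| None after baseline | no value exists | fewer than 3 | baseline (zero change) |
| Week 1 | week-1 rating | 3 of 12 | baseline (zero change) |
| Week 2 | week-2 rating | 6 of 12 | baseline (zero change) |
| Week 3 | week-3 rating | 9 of 12 | baseline (zero change) |
| Week 4 | observed | 12 of 12 | observed |

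A participant who leaves after week 4 has week-4 status at every follow-up visit, up to 16 − 4 = 12 weeks after treatment ended.

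**Weight of one participant.** 1/21 = 4.8 percentage points of an arm's responder rate, if all 21 are treated.

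**Undefined cases at week 4.** If k treated participants per arm have no OTE at all, the difference between arms is undetermined over a width of 2k/21: 9.5 points for k = 1, 19.0 for k = 2, 28.6 for k = 3. To show what the unstated choice can do, assume 13 verum and 7 control responders observed and k = 3 per arm (uncorrected chi-square):

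- left out: 13/18 v 7/18, p = 0.044
- counted as non-responders: 13/21 v 7/21, p = 0.064
- most favourable to verum: 16/21 v 7/21, p = 0.005
- least favourable to verum: 13/21 v 10/21, p = 0.352

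These counts are assumed. They show sensitivity and forecast nothing.

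**Early ratings counted as week-4 response.** Suppose carry-forward gives 14/21 v 7/21: chi-square 4.67, p = 0.031 uncorrected (Fisher 0.063). Suppose four of the counted responders were dropouts with an early favourable rating, and recode them as non-responders:

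- all four in verum: 10/21 v 7/21, chi-square 0.89, p = 0.35
- two in each arm: 12/21 v 5/21, chi-square 4.84, p = 0.028

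The effect depends on how dropout divides between the arms, and the documents give no basis for choosing.

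**Follow-up, one arm.** Assume 60% response at week 4, 40% true response at week 16, and 20% lost at random after week 4. Carry-forward overstates that arm's week-16 rate by 0.20 × (0.60 − 0.40) = 0.04. Counting the missing as non-responders understates it by 0.20 × 0.40 = 0.08.

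**Follow-up, between arms.** With the same random loss d in both arms, the error in the difference is d × (fall in verum − fall in control). It is zero if both arms fall equally. Assume week-4 rates of 60% v 35% and a true 35% in both arms at week 16. The fall is then 25 points v 0, and the spurious difference is 0.10 × 25 = 2.5 points at d = 10% and 0.30 × 25 = 7.5 points at d = 30%.

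**The case against.** The strongest reply is about scope and size, and much of it stands.

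- **Undefined only before week 1.** A reader might infer that the primary outcome cannot be computed for early dropouts in general. It can: weekly OTE gives a value to everyone who reaches week 1. What remains for them is the meaning of a part-treatment rating.
- **No demonstrated reversal.** A reader might take the move from p = 0.031 to 0.35 as the likely damage. It needs all four dropouts in one arm; an even split leaves p = 0.028. The starting p also depends on using the uncorrected test.
- **Follow-up is secondary, and the error may cancel.** A reader might infer that durability is overstated by as much as 4/21 = 19 points. That figure is for one arm and needs all four lost participants to be relapsers. Similar loss and relapse in both arms would largely cancel in the comparison. The direction also reverses if late improvement outweighs relapse.
- **Intervals.** A reader might add that single imputation makes the intervals too narrow. No amount can be attached here, and counting the missing as non-responders is single imputation too. On the figures above it errs by 8 points at week 16 against 4 for carry-forward, so it should not be the main follow-up method.
- **Per-protocol set and pilot status.** The per-protocol analysis gives a partial contrast that rests less on early ratings, but it selects on behaviour after randomization and is not a missing-data method. This is a 42-person convenience-sample pilot, which lowers the stakes; it still tests efficacy and feeds a later sample size.

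An analysis plan that is not shown might add sensitivity analyses, and their absence from the article is not the criticism. The article itself fixes carry-forward for the ITT efficacy analyses, and that stated choice is what is questioned.

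**Conclusion.** The point holds as a weakness in a stated rule. For the week-4 OTE, carry-forward has no value for treated participants who leave before the first rating, and it relabels week-1 to week-3 ratings as end-of-treatment results for later dropouts. For the secondary follow-up outcomes it assumes that week-4 status persists for up to 12 weeks off treatment. For NDI and HADS it sets dropouts before week 4 to zero change.

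The size and direction of the bias are unknown, because the documents give no dropout rate and no split by arm. The one firm figure is 4.8 points of an arm's responder rate per participant; every p-value and bias figure above rests on assumed counts or rates. A reader might conclude that the rule favours acupuncture or invalidates the primary comparison. Nothing in the documents supports either inference. This should be fixed, as a cheap improvement rather than a bar to the trial.

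**What to change.** Before unblinding, replace the carry-forward sentence in Statistical analysis with rules by outcome:

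1. **OTE at week 4 (primary).** Count a treated participant without a week-4 rating as a non-responder. Add a sensitivity analysis by multiple imputation from the weekly OTE and symptom scores, or best- and worst-case bounds.
2. **OTE at weeks 8, 12 and 16.** Do not carry week-4 values forward. Use multiple imputation or a likelihood-based repeated-measures model on observed data, with missing counted as non-response as a sensitivity analysis only.
3. **Symptoms, NDI and HADS.** Use a baseline-adjusted mixed model on all observed data with a simple covariance structure. Seven post-baseline symptom visits would need 7 × 8 / 2 = 28 parameters if unstructured, too many for 42 participants.

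The cost is one paragraph of analysis wording and a little more analysis work. No new visits or data are needed, since the weekly OTE and symptom scores are already scheduled. The downside is that week-4 responder rates may look slightly lower in both arms.

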#### Symptoms assessment

The eight dyspepsia symptoms including postprandial fullness, early satiation, upper abdominal bloating, epigastric pain, epigastric burning, nausea, vomit, and belching will be assessed at baseline, once a week for four weeks in the treatment period and at weeks 8, 12, and 16 after randomization. The severity of each symptom is rated as a four-item questionnaire: asymptomatic (0 points); mild (1 point); moderate (2 points); or severe (3 points) [20]. A higher score reflects a more serious disease state.

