#### Depression and anxiety assessment

Depression and anxiety symptoms will be assessed by the Hospital Anxiety Depression Scale (HADS), which has been validated for in a wide variety of general medical patients. It is a self-report inventory consisting of 14 questions, seven of which relate to anxiety symptoms and seven to depressive symptoms. A higher score reflects a more serious state of depression and anxiety. The participants will complete the HADS at baseline and at weeks 4, 8, and 16 after randomization.

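### The t-test fixed for the continuous secondary outcomes is valid but less efficient than adjusting for the baseline scores the trial already collects

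*Protocol article*

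**What the plan says.** The Statistical analysis section sets one rule for all outcomes: "Continuous variables will be analyzed using the t-test and categorical variables using the Chi-square". It adds that "The statistical significance level will be set at 0.05 (two-sided) with 95% confidence intervals". No covariate or repeated-measures model is named, and the text does not say whether the t-test is applied to follow-up scores or to changes from baseline.

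The continuous outcomes all have baseline values:
- The eight symptoms, each scored 0 to 3, "will be assessed at baseline, once a week for four weeks in the treatment period and at weeks 8, 12, and 16 after randomization".
- NDI is measured at baseline and at weeks 4, 8 and 16 (Disease-specific QoL assessment).
- For anxiety and depression, "The participants will complete the HADS at baseline and at weeks 4, 8, and 16 after randomization".

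Table 3 shows the same schedule. On numbers, the Sample size section says "We did not perform a sample size calculation for this pilot study, but will use a convenience sample" and "Both the verum acupuncture and minimal acupuncture groups will contain 21 eligible participants". That section gives efficacy as an aim alongside feasibility and says the results will help to size later trials. The primary outcome is the OTE responder rate at week 4, which is binary and is itself a comparison with the pre-treatment state.

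**The concern.** When an outcome is measured before and after treatment, the baseline score usually predicts part of the follow-up score. A t-test on follow-up scores leaves that predictable part in the error term. A t-test on change scores removes it with a fixed slope of 1, which is generally too steep and adds noise when the correlation is low. ANCOVA estimates the slope from the data and is usually at least as precise as either.

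At stake are wider confidence intervals and lower power for symptoms, quality of life and mood in a trial of 42 patients. This is more than a formality here. The Discussion says the study is to evaluate whether acupuncture improves postprandial fullness and early satiation, and those two symptoms are scored individually only among the secondary outcomes. The protocol itself names the t-test, so this is not a detail it leaves open for an analysis plan.

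**Working it through.** **The plan's own figure.** The only figure is the sample size: 3 centres × 14 = 42 = 2 × 21. It is consistent. No power, effect size or SD is stated, so there is no power calculation to reproduce.

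**Inputs from the protocol article.** n = 21 per arm; two-sided alpha = 0.05; baseline available for symptoms, NDI and HADS.

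**Assumptions, not in the document.** A true difference of 0.7 SD; equal SDs at baseline and follow-up; baseline-to-follow-up correlation r from 0 to 0.6; no dropout; roughly normal scores.

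**Formulas.** The variance of the estimated difference, in units of 2·SD²/n, is:
- t-test on follow-up scores: 1
- t-test on change scores: 2(1 − r)
- ANCOVA: (1 − r²) × [1 + 1/(2n − 4)] = (1 − r²) × (1 + 1/38) = (1 − r²) × 1.026

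The factor 1.026 is the price of estimating the slope. Power comes from the noncentral t distribution with noncentrality 0.7 / √(V × 2/21), where V is the variance factor above. It has 40 degrees of freedom for the t-tests and 39 for ANCOVA.

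**Example at r = 0.5.** Follow-up-score t-test: √(2/21) = 0.309, noncentrality 0.7/0.309 = 2.27, power 60%. ANCOVA: V = 0.75 × 1.026 = 0.770, noncentrality 2.27/√0.770 = 2.59, power 71%.

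**Results at 0.7 SD.**

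| r | V, change score | V, ANCOVA | Power, follow-up t-test | Power, change t-test | Power, ANCOVA |
|---|---|---|---|---|---|
| 0 | 2.00 | 1.026 | 60% | 35% | 59% |
| 0.2 | 1.60 | 0.985 | 60% | 42% | 61% |
| 0.3 | 1.40 | 0.934 | 60% | 46% | 63% |
| 0.4 | 1.20 | 0.862 | 60% | 52% | 66% |
| 0.5 | 1.00 | 0.770 | 60% | 60% | 71% |
| 0.6 | 0.80 | 0.657 | 60% | 70% | 78% |

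**Equivalent size.** To match ANCOVA on 21 per arm, a follow-up-score t-test would need 21/V per arm: about 22, 24, 27 and 32 at r = 0.3, 0.4, 0.5 and 0.6.

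**Precision.** The 95% CI half-width is 0.62 SD for the follow-up-score t-test at any r. For ANCOVA it is 0.60, 0.58, 0.55 and 0.51 SD at r = 0.3, 0.4, 0.5 and 0.6.

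**Break-even.** ANCOVA matches the follow-up-score t-test when (1 − r²) × 1.026 = 1, that is, at r of about 0.16. It beats the change-score t-test when (1 + r)/2 × 1.026 < 1, that is, for r below about 0.95.

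**Check by simulation.** With 20,000 simulated trials per correlation and a true difference of 0.8 SD, power for ANCOVA was 74%, 82% and 94% at r = 0.3, 0.5 and 0.7, against 71% to 72% for the follow-up-score t-test. The formulas give 74%, 82% and 94%, against 72%.

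**The case against.** The strongest reply is that nothing here is invalid. Under randomisation the unadjusted t-test is unbiased and keeps its error rate, and chance baseline imbalance is already part of its standard error. The outcomes concerned are secondary, the study is a pilot with a convenience sample and no power target, and the size of the gain rests on a correlation the document does not give. All of this stands. It limits the point to efficiency, but it does not remove it: the protocol names efficacy as an aim and a 0.05 test, and the better analysis needs no new data.

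A reader might infer more than the document supports:
- **That the plan ignores baseline.** This is so only if follow-up scores are compared. A change-score t-test uses the baseline, and the text does not say which is meant.
- **That baseline imbalance biases the comparison.** It does not; it adds variance that the standard error reflects.
- **That the primary conclusion is weakened.** The OTE responder rate has no baseline score to adjust for.
- **That centre must also enter the model, or that OTE needs a centre-stratified analysis.** The randomisation section mentions no stratification by centre, so the design as described does not require it. Two further centre parameters also have a cost: if centre explains nothing, power at r = 0.3 falls back to about 60%, the t-test's own figure.
- **That the next trial would be wrongly sized.** The residual SD and the correlation can be computed from the same data whichever test is used. Using the raw SD would only make a baseline-adjusted trial larger than necessary.

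Finally, single symptoms scored 0 to 3 are ordinal, so the SD-based figures fit NDI, HADS and a summed symptom score better than individual items.

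**Conclusion.** The point holds as one of efficiency in the secondary outcomes. Whichever t-test is meant, ANCOVA is more precise over the plausible middle range of correlations. At an assumed 0.7 SD and r from 0.3 to 0.6, it adds about 3 to 18 percentage points of power over a follow-up-score t-test. Over a change-score t-test it adds about 8 to 16 points. Against the follow-up-score version the advantage is negligible at r of about 0.2 or below, and at r = 0 it becomes a loss of about 2.6% in variance. These sizes depend on the assumed effect, equal SDs and the assumed correlation. The document supports no claim of bias, of an inflated error rate, or of harm to the primary analysis. The change is worth making, but the planned tests are not unsound without it.

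**What to change.** For NDI, HADS and a summed symptom score (eight items of 0 to 3, so 0 to 24), replace the t-test with ANCOVA of the follow-up score on treatment, with the baseline score of the same measure as covariate. A mixed model for repeated measures with baseline, visit, arm and arm-by-visit is an acceptable alternative that uses all visits. Report the adjusted difference with its 95% CI. Report also the residual SD and the baseline-to-follow-up correlation, so that the next trial can be sized for the analysis it will use. Leave the OTE analysis as it is on this point.

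The cost is one degree of freedom for the covariate and slightly more analysis work. The data are already scheduled for collection and the named software can fit these models. The article gives the trial status as recruiting; the change should be dated and made before unblinding.
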